## Abstract

**Background:**

Obese patients undergoing general anesthesia and mechanical ventilation during laparoscopic abdominal surgery commonly have a higher incidence of postoperative pulmonary complications (PPCs), due to factors such as decreasing oxygen reserve, declining functional residual capacity, and reducing lung compliance. Pulmonary atelectasis caused by pneumoperitoneum and mechanical ventilation is further aggravated in obese patients. Recent studies demonstrated that individualized positive end-expiratory pressure (iPEEP) was one of effective lung-protective ventilation strategies. However, there is still no exact method to determine the best iPEEP, especially for obese patients. Here, we will use the best static lung compliance (Cstat) method to determine iPEEP, compared with regular PEEP, by observing the atelectasis area measured by electrical impedance tomography (EIT), and try to prove a better iPEEP setting method for obese patients.

**Methods:**

This study is a single-center, two-arm, prospective, randomized control trial. A total number of 80 obese patients with body mass index ≥ 32.5 kg/m^2^ scheduled for laparoscopic gastric volume reduction and at medium to high risk for PPCs will be enrolled. They will be randomly assigned to control group (PEEP5 group) and iPEEP group. A PEEP of 5 cmH_2_O will be used in PEEP5 group, whereas an individualized PEEP value determined by a Cstat-directed PEEP titration procedure will be applied in the iPEEP group. Standard lung-protective ventilation methods such as low tidal volumes (7 ml/kg, predicted body weight, PBW), a fraction of inspired oxygen ≥ 0.5, and recruitment maneuvers (RM) will be applied during and after operation in both groups. Primary endpoints will be postoperative atelectasis measured by chest electrical impedance tomography (EIT) and intraoperative oxygen index. Secondary endpoints will be serum IL-6, TNF-α, procalcitonin (PCT) kinetics during and after surgery, incidence of PPCs, organ dysfunction, length of in-hospital stay, and hospital expense.

**Discussion:**

Although there are several studies about the effect of iPEEP titration on perioperative PPCs in obese patients recently, the iPEEP setting method they used was complex and was not always feasible in routine clinical practice. This trial will assess a possible simple method to determine individualized optimal PEEP in obese patients and try to demonstrate that individualized PEEP with lung-protective ventilation methods is necessary for obese patients undergoing general surgery. The results of this trial will support anesthesiologist a feasible Cstat-directed PEEP titration method during anesthesia for obese patients in attempt to prevent PPCs.

**Trial registration:**

www.chictr.org.cn ChiCTR1900026466. Registered on 11 October 2019

## Background

It is quite certain that postoperative pulmonary complications (PPCs) result in more morbidity and mortality, as well as prolong hospital stays. According to the type of surgery and the definition of PPCs, the incidence of PPCs has been reported to range from 5 to 33% [1, 2]. Considering that approximately 234 million patients worldwide require surgical treatment under general anesthesia each year [3], reducing the incidence of PPCs may have a great impact on global mobility and mortality. In recent years, more and more attention is paid to intraoperative mechanical ventilation strategies, which may affect PPCs in addition to the preoperative optimization of patients’ status and operation style.

Recently, an international expert consensus recommendation about lung-protective ventilation for the surgical patient was reported [4]. In the expert consensus, the following was strongly recommended: preoperative pulmonary risk evaluation, an individualized mechanical ventilation which include a tidal volume (*V*_*T*_) of 6–8 ml/kg predicted body weight (PBW), positive end-expiratory pressure (PEEP) of 5 cmH_2_O, and alveolar recruitment maneuvers (RM). Among these lung-protective ventilation strategies, individualized PEEP is important to prevent processive alveolar collapse. RM can reverse alveolar collapse but have limited benefit without sufficient PEEP. However, how to set individualized PEEP remains a matter of debate.

Obese patients have a high risk of PPCs. In obese patients, lung function is impaired due to the reduction of oxygen reserve, functional residual capacity, and lung compliance. Especially in the general anesthesia of laparoscopic surgery, the formation of atelectasis caused by pneumoperitoneum and mechanical ventilation will be further aggravated, which will seriously affect the prognosis and outcome of obese patients [5–7]. In order to reduce the incidence of atelectasis, the PEEP level of obese patients should be much higher than that of non-obese patients [8, 9]. However, how to set up the ideal individualized PEEP for obese patients in laparoscopic surgery is still uncertain. In the past clinical practice, the PEEP value was often set at 5–10 cmH_2_O based on personal experience or according to the results of numerous studies applied to the optimal PEEP in non-obese patients. It was confirmed that the protective effect of generalized and empirical PEEP on lung function was much lower than that of individualized PEEP [9–11]. Nestler and colleagues [11] evaluated the effect of individualized PEEP titrated by electrical impedance imaging (EIT) in obese patients undergoing laparoscopic surgery. They found that compared with normal PEEP group, the iPEEP group reduced atelectasis, decreased ventilator driving pressure, and improved oxygenation in obese patients. And the iPEEP titrated by EIT was up to 18.5 cmH_2_O, which is far more than our routine used. Eichler [12] reported the results of using esophageal pressure measurement and EIT to adjust PEEP; they found an average iPEEP of 23.8 cmH_2_O was necessary. However, the iPEEP titration using electrical impedance imaging or esophageal pressure measurement is not always feasible in routine clinical practice [13]. Therefore, we need to find some simple methods of iPEEP titration with high clinical feasibility in obese patients.

It had been confirmed that there was a very clear correlation between the severity of inflammatory reaction and the concentration of serum procalcitonin (PCT) [14, 15]. Therefore, it is rational to believe that the inflammatory response can be monitored by regular PCT measurements during the perioperative period; hence, PCT kinetic monitoring can be used as an indicator of host inflammatory response.

This trial will verify the following hypothesis: individualized PEEP titrated by the best static lung compliance (Cstat), combined with other lung-protective ventilation strategies, compared with the conventional setting of PEEP, can reduce atelectasis and PPCs in obese patients at intermediate to severe risk for PPCs. Through evaluation of atelectasis and ventilation distribution by electrical impedance tomography (EIT) of obese patients before and after laparoscopic surgery, we confirm the effect of iPEEP on oxygenation and postoperative PPCs in obese patients. Meanwhile, we observe the changes of perioperative pulmonary inflammatory factors and other health indicators (length of stay, hospital costs), so as to confirm its effectiveness and significance of iPEEP in reducing postoperative pulmonary complications in obese patients.

## Methods/design

### Objectives and design

This prospective, single-center, randomized, controlled, single-blind (patient-blinded, investigator-blinded) trial tests the hypothesis that individualized PEEP titrated by Cstat is an ideal lung-protective strategy for laparoscopic surgery in obese patients at intermediate and severe risk for PPCs. In total, 80 patients will be randomly assigned to one of two different intraoperative mechanical ventilation strategies (see Consolidated Standards of Reporting Trials [CONSORT] diagram, Fig. 1). The SPIRIT 2013 Checklist is given in Additional file 1.

**Fig. 1 Fig1:**
[figure not shown]
Consolidated Standards of Reporting Trials (CONSORT) diagram for this trail. PEEP, positive end-expiratory pressure; iPEEP, individual PEEP, COPD, chronic obstructive pulmonary disease, ICU, intensive care unit; ASA, American Society of Anesthesiologists classification, PaO_2_, partial pressure of arterial oxygen, FiO_2_, inspiratory fraction of inspired oxygen, EIT, electrical impedance tomography, PPCs, postoperative pulmonary complications, PCT, procalcitonin

This study will be conducted at the Beijing Friendship Hospital affiliated to Capital Medical University, China. The trial will be conducted according to the WMA of the Declaration of Helsinki and the CIOMS Principles of the International Guidelines for Biomedical Research Involving Human Subjects. This study has been approved by the Ethics Committee of the Beijing Friendship Hospital (the approval number from the Ethics Committee is 2019-P2-137-02) and has been registered in the Chinese Clinical Trial Registry (Chictr) (registration number: ChiCTR1900026466).

### Blinding, data collection, randomization, and record keeping

This is a single-blind study, participants are blinded, implementers are not blinded, and observers are blinded. Patients’ data, respiratory parameters, anesthesia data, fluid balance, laboratory results, postoperative clinical status, length of hospitality, and cost will be collected on case report forms (CRF).

All participants who meet the inclusion criteria are randomly divided into two groups, iPEEP group and PEEP5 group in a ratio of 1:1. Randomization will be performed by a computer-generated randomization table, with 20 blocks of four patients per block. Distribution will be stored in numbered, sealed, and opaque envelopes. Participants will be included and assigned in numerical order. All original records (informed consent, CRF, and related letters) will be archived and protected for 10 years, and then destroyed according to the hospital standards.

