### Standard procedures

In order to avoid interference with the trial intervention, perioperative anesthesia care (including induction and maintenance of general anesthesia, postoperative pain management, and fluid management) is performed by a relatively fixed anesthesia team according to clinical routine. The following approaches are suggested:
Adequate airway assessment is required in all patients, predicated on 12 predictors of a difficult airway, and when more than three predictors are present, consideration should be given to intubating the trachea with an awake endotracheal tube or with slow induction to preserve spontaneous breathing, establishing an airway and preparing adequate equipment, personnel, and drugs in advance (Attached Table 1: Predictors of Difficult Airway).Patients are routinely monitored after admission in the operating room, such as blood pressure, electrocardiogram, pulse oxygen saturation, BIS, and urine volume. Invasive arterial pressure was monitored by radial or dorsalis pedis artery puncture under local anesthesia.For patients without anticipated difficult airway, rapid sequence induction was used for anesthesia induction: midazolam 0.05 mg/kg is given 15 min before induction, anesthesia is induced with etomidate, sufentanil, rocuronium, or cisatracurium, and mechanical ventilation was performed after tracheal intubation.Anesthesia is maintained with total intravenous anesthesia by using intravenous propofol and remifentanil.The maintenance of intraoperative circulation is actively managed based on surgery procedure and bleeding.Perform postoperative pain treatment to control a visual analogue scale (VAS) pain score < 3. Local incision anesthesia or neuraxial block should be performed.Encourage early mobilization, deep breathing exercises, and stimulation of cough in the postoperative period.

Data on the procedures applied will be recorded in detail and analyzed. All anesthesia and related treatment need to comply with clinical routines. Nasogastric tubes and intravenous catheters may be used according to surgery practice or guidelines. Urinary bladder catheter is usually not inserted according to the routine for this type of surgery in our hospital.

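### Fixed blocks of four with unblinded implementers: up to a third of allocations could be deduced in advance by anyone who knows the block size and the earlier allocations

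*Protocol article*

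**What the plan says.** The section on blinding, data collection, randomization and record keeping fixes the method: "Randomization will be performed by a computer-generated randomization table, with 20 blocks of four patients per block". The arms are the "iPEEP group and PEEP5 group in a ratio of 1:1". On concealment and order it says "Distribution will be stored in numbered, sealed, and opaque envelopes" and "Participants will be included and assigned in numerical order". No stratification factor is named, so the text reads as one sequence for the site.

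On blinding, the same section says "participants are blinded, implementers are not blinded, and observers are blinded". The Objectives and design section calls the study a "This prospective, single-center, randomized, controlled, single-blind (patient-blinded, investigator-blinded) trial", and the word investigator there sits awkwardly with implementers who are not blinded. Under Standard procedures, perioperative anaesthesia care is "performed by a relatively fixed anesthesia team according to clinical routine".

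Study population places screening and recruitment at the routine preoperative assessment. Trial status reports 36 participants recruited and the trial ongoing when the article was written.

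**The concern.** With one fixed block size and a 1:1 ratio, each group of four consecutive patients must contain two of each arm. Anyone who knows the size and has seen the earlier allocations in a block can work out the last one every time, and the third whenever the first two match. The arm cannot be hidden from those who ventilate the patient, since one arm stays at a fixed PEEP and the other is titrated stepwise. A relatively fixed team at one centre is likely to see successive allocations. The block size itself is now in print, in an article written while 44 patients were still to be recruited.

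What is at stake is allocation concealment. Surgery is scheduled, so a person who foresees the next arm has some freedom over whom to approach and in what order. Blinded observers do not protect against this, because the selection would act before any outcome is assessed.

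**Working it through.** **Inputs**
- Block size 4, 20 blocks, 1:1, used in numerical order (section on blinding and randomization).
- Total 80 (Objectives and design). Recruited at the time of writing: 36 (Trial status), leaving 80 − 36 = 44.
- Assumption, not stated in the article: the person predicting knows the block size and all earlier allocations in the block.

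**The plan's own figure.** 20 blocks × 4 = 80, which matches the stated total. There is no arithmetic error in the list.

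**Allocations known with certainty.** A 1:1 block of four has 4!/(2! 2!) = 6 equally likely orders. An allocation is determined once one arm has used its two places.
- Positions 1 and 2: never determined.
- Position 3: determined if the first two match (AABB, BBAA), so 2/6 = 1/3.
- Position 4: always determined.

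The expected number per block is 1 + 1/3 = 4/3, and (4/3)/4 = 33.3%. Over the whole list this is 20 × 4/3 = 26.7 of 80. Each block contributes 1 (probability 2/3) or 2 (probability 1/3), with variance 2/9. The SD over 20 blocks is therefore √(20 × 2/9) = 2.1, and the possible range is 20 to 40. For the remaining 44 patients, 44/3 = 14.7, or about 15.

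**Best guess.** Always guess the arm with more places left in the block.
- Position 1: 1/2.
- Position 2: 2/3.
- Position 3: 1/3 × 1 + 2/3 × 1/2 = 2/3.
- Position 4: 1.

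The sum is 2.833 of 4, or 70.8%, which is 56.7 of 80. Chance alone gives 50%.

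**Alternatives.** The fixed sizes were enumerated in the same way. The varied sizes were simulated with a predictor who knows the set of sizes (each equally likely) but not their order, and who updates the probabilities after each allocation.

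| Scheme | Known with certainty | Best guess correct |
|---|---|---|
| Fixed 4 (as planned) | 33.3% | 70.8% |
| Fixed 6 | 25.0% | 68.3% |
| Fixed 8 | 20.0% | 66.6% |
| Random 4/6, 80 patients | 5.5% | 69.1% |
| Random 4/6/8, 80 patients | 2.2% | 67.9% |
| Random 4/6/8, 44 patients | 2.4% | 67.6% |

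Varying the size removes most of the certainty and little of the guessing advantage.

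**Imbalance.** Part-way through a block, the arms can differ by at most half the block size: 4/2 = 2 as planned, and 8/2 = 4 with sizes up to 8.

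**The case against.** The strongest reply is that the link from predictability to enrolment is not in the text. The sentence on assignment in numerical order is passive and names nobody. Recruitment happens at preoperative assessment, and nothing says that the ventilating anaesthetists do it. If recruiters are separate from implementers, or if several elective patients consent before earlier ones are treated, fewer than a third of allocations are predictable. Who holds the envelopes and who enrols is detail that a condensed article may leave to the full protocol, so silence cannot be read in the least favourable way. This stands: one third is what a fully informed recruiter would reach on average, and the point must be conditional.

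Two further replies also stand. Eligibility rests mostly on fixed thresholds (BMI, age, ASA class, ARISCAT score), which limits discretion over who qualifies, though not over timing or order. BMI, preoperative risk, baseline EIT and oxygenation before induction are recorded, so imbalance in these could be seen and adjusted for. Selection on unmeasured features could not.

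It is also true that varied blocks lower best-guess accuracy only from 71% to about 68%. Someone content to act on a good guess would lose little. The gain lies in removing certainty.

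A reader might go further and infer that the trial is unblinded, or that the treating team does know a third of the allocations before enrolment and so the comparison is biased. The documents do not support either. Participants and observers are blinded, the team is described as relatively fixed and not as small, and nothing shows that anyone used foreknowledge. A reader might also take 36 recruited as nine completed blocks. The article does not say that all 36 were randomised.

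The remaining core is not an omission. The article states one fixed block size, and sealed envelopes hide only the next card, not what the earlier cards imply.

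**Conclusion.** The point holds as a conditional design weakness. Under the stated scheme, a person who knows the block size and the earlier allocations can deduce 33% of allocations on average (about 27 of 80, never fewer than 20; about 15 of the 44 outstanding) and guess 71% correctly. This rests on a 1:1 ratio within every block, a single unstratified sequence, and enrolment or scheduling by someone with that knowledge. The last condition is plausible at one centre with a relatively fixed team and a published block size, but it is not established. The consequence is a risk of selection bias that baseline adjustment could only partly address. Sample size and power are unaffected.

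**What to change.** For patients not yet randomised, replace the unused envelopes from the next completed block onward. The new list should use randomly varied block sizes, for example 4, 6 and 8. Keep the set and order of sizes from staff who enrol or treat, in a document they do not see. Confirm the block boundary from the randomisation log, not from the recruitment count in the article.

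The change takes certain predictions from 33% to about 2%, and best-guess accuracy from 71% to about 68%. It costs one new list and one set of envelopes, and the largest possible imbalance within a block rises from 2 to 4. It changes nothing in the treatment of patients and helps only those still to be randomised when it is made. The planned recruitment end of December 31, 2020 limits how many that is.

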### Study population

Obese patients scheduled for laparoscopic metabolic and bariatric surgery will be screened and recruited during routine preoperative assessment. Participants meeting the inclusion criteria will be asked for signed informed consent. Inclusion criteria are as follows: BMI ≥ 32.5, 18–60 years old, American Society of Anesthesiologists (ASA) physical status I–III, and moderate or high risk for postoperative pulmonary complications. To identify patients at risk for PPCs, the Assess Respiratory Risk in Surgical Patients in Catalonia (ARISCAT) score is used [16]. This score predicts preoperative risk for PPCs using seven independent predictors, four of which are patient-related and three of which are surgery-related. An ARISCAT risk score ≥ 26 is associated with an intermediate to high risk for PPCs (Assess Respiratory Risk in Surgical Patients in Catalonia, ARISCAT ≥ 26) (Additional Fig 1). According to the Asia-Pacific classification, here, we used BMI ≥ 32.5 as the obese patient’s definition [17].

The exclusion criteria are as follows: patients aged < 18 years or > 60 years, ASA grade ≥ IV, severe chronic obstructive pulmonary disease (COPD, GOLD grades III–IV), a history of severe or uncontrolled bronchial asthma, patients with pulmonary metastases, ongoing renal replacement therapy before surgery, congestive heart failure (NYHA grades III–IV), and patients who cannot be extubated in time after surgery and need to return to the ICU with an endotracheal tube. For the specific clinical trial process, see Fig. 1.

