### Intervention

After induction of anesthesia in all patients, PEEP was maintained at 5 cmH_2_O, mechanical ventilation was performed for 5 min, and baseline measurements of relevant parameters were performed in all patients. In the PEEP5 group, 5 cmH_2_O PEEP was maintained throughout the mechanical ventilation. Ventilator-driven alveolar recruitment maneuver (RM) is performed three times in both groups. In both groups, the first RM is performed at the moment of 5 min after intubation, the second RM is performed at the moment of establishment of pneumoperitoneum, and the third RM is at the moment before extubation. The ventilator-driven alveolar recruitment maneuver is performed as following steps [18] (Fig. 2):
In pressure control mode, the driving pressure is set to 15–20 cmH_2_O.Starting at a PEEP of 5 cmH_2_O and increasing in steps of 5 cmH_2_O, each increase was maintained for 30 s until it was increased to a PEEP of 20 cmH_2_O, with a inspiratory plateau pressure as high as 40 cmH_2_O. Maintain 5 breaths at PEEP = 20 cmH_2_O to the end.During the whole period of RM, *V*_*T*_ is 7 ml/kg, and I:E is 1:1.Ppeak < 55 cmH_2_O.A standardized fluid therapy regimen was used in all patients, and during RM, patients were given according to the protocol, along with vasopressors, to maintain MAP > 70 mmHg and minimize short-term hemodynamic suppression during RM.

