**Fig. 2 Fig2:**
[figure not shown]
The ventilator-driven alveolar recruitment maneuver protocol. Ppeak, peak airway pressure; Pplat, plateau airway pressure; PEEP, positive end-expiratory pressure; *V*_*T*_, tidal volume normalized for adjusted body weight; I:E, ratio between inspiratory and expiratory time; RR, respiratory rate

The iPEEP group obtained iPEEP for this patient by following these steps (Fig. 3):
First RM1: At 5 min after intubation, the first RM is performed.Set airway peak pressure not to exceed 55 cmH_2_O.*V*_*T*_ to 7 ml/kg (adjusted body weight, ABW), respiratory rate 12–15 breaths/min, I: E to 1:1.Titration process: At the moment of establishment of pneumoperitoneum, we begin to titrate the iPEEP (Fig. 4). Setting initial PEEP to 5 cmH_2_O, increasing PEEP according to the gradient of 2 cmH_2_O every 3 min, calculating Cstat (according to the formula: Cstat = *V*_*T*_/Plat-PEEP). Gradually increasing PEEP, until the calculated Cstat shows a downward trend, set its previous PEEP (corresponding to PEEP for high Cstat) as the optimal iPEEP for this patient.The highest PEEP is limited to 20 cmH_2_O.After setting the iPEEP, the second RM2 is performed.Before extubation, the third RM3 is performed.

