Mild respiratory failure: PaO_2_ < 60 mmHg or SpO_2_ < 90%, effective for oxygen response of 2 L/min, except for low ventilation, at least 10 min under air inhalation.Moderate respiratory failure: PaO_2_ < 60 mmHg or SpO_2_ < 90%, effective only for oxygen response of > 2 L/min, except for low ventilation.Severe respiratory failure: requiring support of mechanical ventilation or invasive ventilation.ARDS: ARDS according to Berlin definition.Bronchospasm (newly detected expiratory wheezing treated with bronchodilators).New pulmonary infiltrative inflammation (confirmed by chest X-ray, but no other clinical signs).Pulmonary infection (new or progressive radiographic infiltrate plus at least two of the following: antibiotic treatment, tympanic temperature > 38 °C, leukocytosis or leukopenia [white blood cell count < 4000 cells/mm^3^ or > 12,000 cells/mm^3^], and/or purulent secretions).Aspiration pneumonitis (respiratory failure after the inhalation of regurgitated gastric contents).Pleural effusion (chest X-ray demonstrating blunting of the costophrenic angle, loss of the sharp silhouette of the ipsilateral hemidiaphragm in upright position, evidence of displacement of adjacent anatomical structures, or [in supine position] a hazy opacity in one hemithorax with preserved vascular shadows).Atelectasis (lung opacification with shift of the mediastinum, hilum, or hemidiaphragm toward the affected area, as well as compensatory overinflation in the adjacent nonatelectatic lung).Cardiopulmonary edema (clinical signs of congestion, including dyspnea, edema, rales, and jugular venous distention, with chest X-ray demonstrating increase in vascular markings and diffuse alveolar interstitial infiltrates).Pneumothorax (air in the pleural space with no vascular bed surrounding the visceral pleura).

One of the above conditions was defined as positive for PCCs.

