### Statistical analysis

After the trial, the research team will work with medical statisticians to analyze the data. Statistical analysis will be based on intention to treat. SPSS 20.0 statistical software was used for analysis.

The most of the source data will be recorded onto the CRF; however, before data analyzing, the pattern of missing data will be evaluated. The analysis of the graphics and data obtained by the EIT machine will be conducted by a special computer expert familiar with machine principles.

All data distribution will be detected by Kolmogorov-Smirnov analysis. Normal distribution data will be represented by mean and standard deviation (SD), and skewed data will be represented by median (quartile range). Compared with the related samples, *t* test will be used for normal distribution data; Wilcoxon signed-rank test and Mann-Whitney *U* test will be used for skewed data. The difference in proportions will be evaluated using Fisher’s exact test and the risk ratio of the associated 95% confidence interval (CI). The data of VAS score, ICU days, hospitalization days, and hospitalization costs will be analyzed by chi-square test. *P* value < 0.05 will be considered significant.

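### Excluding patients who leave surgery intubated is a post-randomisation exclusion that conflicts with intention to treat and may bias the comparison in either direction

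*Protocol article*

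**What the plan says.** The exclusion criteria (protocol article, Study population) end with "patients who cannot be extubated in time after surgery and need to return to the ICU with an endotracheal tube". The other items on that list (age, ASA grade, lung, heart and renal conditions) can be established before surgery.

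The sequence of events is as follows:

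- **Recruitment.** Patients "will be screened and recruited during routine preoperative assessment" (Study population).
- **Randomisation.** "All participants who meet the inclusion criteria are randomly divided into two groups, iPEEP group and PEEP5 group in a ratio of 1:1" (Blinding, data collection, randomization, and record keeping).
- **Control arm.** "In the PEEP5 group, 5 cmH_2_O PEEP was maintained throughout the mechanical ventilation" (Intervention).
- **iPEEP arm.** "At the moment of establishment of pneumoperitoneum, we begin to titrate the iPEEP" (Intervention, steps listed after Fig. 2).
- **Analysis.** "Statistical analysis will be based on intention to treat" (Statistical analysis).

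The PPC definition (Study endpoints) includes "Severe respiratory failure: requiring support of mechanical ventilation or invasive ventilation", and closes with "One of the above conditions was defined as positive for PCCs". ICU stay, hospital stay and hospital costs are also listed as outcomes.

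**The concern.** An eligibility rule should depend only on what is known before allocation. This one depends on an event that follows the allocated ventilation and that the ventilation could affect, since the hypothesis is that iPEEP reduces atelectasis and PPCs. Applied as written, it takes randomised patients out of the trial, which an intention-to-treat analysis does not allow.

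The event also overlaps the outcomes. A patient sent to the ICU intubated and ventilated fits the severe respiratory failure wording and will usually add ICU and hospital days. If such removals differ by arm, the groups compared are no longer those formed by randomisation. Equal removals can still change a risk ratio.

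There is also room for discretion. The protocol does not define what counts as extubation in time, and those delivering the intervention are not blinded. A decision to exclude could therefore be made with knowledge of the arm.

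**Working it through.** **1. Timing.** The article does not give the exact moment of randomisation. The arms already differ from the establishment of pneumoperitoneum onward, so randomisation must precede any attempt at extubation. The criterion is therefore post-randomisation.

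**2. The plan's own figure.** Inputs from Sample size calculations: collapse 6.2 (SD 4.1) against 10.8 (SD 7.1), difference 4.6, α 0.05 (taken as two-sided), power 0.90.

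n per group = (1.960 + 1.282)² × (4.1² + 7.1²) / 4.6² = 10.51 × 67.22 / 21.16 = 33.4, so 34. With the noncentral t distribution, 35 is the smallest n that reaches 90% (0.903, Welch). Then 35 / 0.90 = 38.9, so 39, and the plan takes 40. The sample size reproduces and is not at issue. With all 40 per arm analysed, power is 0.944 (normal approximation).

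**3. PPC comparison, assumed counts.** The Background quotes a PPC incidence of 5 to 33%. Take 13/40 control and 7/40 iPEEP, with every removed patient PPC-positive.

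- Nobody removed: (7/40)/(13/40) = 0.54
- 4 control, 0 iPEEP removed: (7/40)/(9/36) = 0.70
- 2 removed from each arm: (5/38)/(11/38) = 0.45

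**4. PPC comparison, range of assumed rates.** If p is the true risk and q the fraction removed, all PPC-positive, the observed risk is (p − q)/(1 − q).

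| True risk, control / iPEEP | Removed, control / iPEEP | Risk difference (points) | Risk ratio |
|---|---|---|---|
| 33% / 20% | none | 13.0 | 0.61 |
| | 5% / 0% | 9.5 | 0.68 |
| | 10% / 2.5% | 7.6 | 0.70 |
| | 5% / 5% | 13.7 | 0.54 |
| | 2.5% / 5% | 15.5 | 0.50 |
| 20% / 12% | none | 8.0 | 0.60 |
| | 5% / 0% | 3.8 | 0.76 |
| | 2.5% / 5% | 10.6 | 0.41 |

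More removals among controls make the benefit look smaller. More removals in the iPEEP arm make it look larger.

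**5. EIT collapse, extreme case.** Assume normal data and that those removed are exactly the worst fraction f of controls, with none removed from the iPEEP arm. The control mean falls by 7.1 × φ(z)/(1 − f), where z is the 1 − f quantile.

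| f | Fall in control mean | Share of 4.6 | Difference left | Power |
|---|---|---|---|---|
| 2.5% | 0.43 | 9% | 4.17 | 0.917 |
| 5% | 0.77 | 17% | 3.83 | 0.879 |
| 10% | 1.38 | 30% | 3.22 | 0.771 |

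With 40 controls, 5% is two patients. If the same worst fraction is removed from both arms, the difference left is 4.42, 4.27 or 4.02.

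**The case against.** **The item may be a badly worded screening criterion.** It stands among preoperative items, recruitment is preoperative, and the text does not say that data from randomised patients are deleted. The flow diagram (Fig. 1) is not available here, so the path of these patients cannot be checked. This point stands in part. The literal wording, however, describes a failure that has occurred after surgery, and no visible text keeps such patients in the analysis. On either reading the criterion and the intention-to-treat statement must be reconciled.

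**The illustrations rest on chosen inputs.** This stands. Four against none would mean 10% of controls leaving surgery intubated and no iPEEP patients, in a population of ASA I–III aged 18–60. No figure in the article supports that. The EIT case also assumes that the patients removed have exactly the worst collapse values, and only in one arm. PPC is a secondary endpoint.

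**Stronger readings.** A reader might infer that the analysis is biased, or that it loses its most severe respiratory failures. The article supports neither. It gives no failure rate, no count by arm and no report of any removal, and if no such event occurs there is no bias. Patients who are extubated and later ventilated again still count as PPC-positive, and failure to extubate can have non-respiratory causes.

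**Deleting the item does not recover the primary data.** This stands. One oxygenation sample (T4) is defined as 20 minutes after extubation, and the Mechanical ventilation section places the second EIT recording after extubation. A patient still intubated at two hours has neither value as defined, with or without the criterion.

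**Conclusion.** The point holds as a defect in the rule. The criterion is a post-randomisation event that the allocated ventilation can affect, it conflicts with the stated intention-to-treat analysis, and it partly overlaps one PPC component and the length-of-stay outcomes. It creates a risk of bias in either direction, and the article does not show that bias has occurred.

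The size cannot be determined from the article. Under the assumed inputs above, a true PPC risk ratio of about 0.6 could appear as anything from 0.41 to 0.76. In the extreme EIT case, removing two of 40 controls takes away 17% of the planned difference. These figures show only that a handful of exclusions matters with 40 patients per arm.

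The most direct effect is on PPCs, ICU stay, hospital stay and cost. For the two primary endpoints the problem is mainly values missing because of the event. The dropout allowance can cover these in number, but it does not remove the bias.

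**What to change.** - Delete this item from the exclusion criteria. Keep every randomised patient in the allocated arm, including any already removed under the rule. The article reports 36 recruited and the trial ongoing, so this can be settled before analysis.
- Count a patient who meets the protocol's own severe respiratory failure wording as PPC-positive. Include the patient's ICU stay, hospital stay and costs, and report the number leaving surgery intubated, with the cause, by arm.
- Treat T4 oxygenation and post-extubation EIT in these patients as missing because of the event. Do not pool EIT taken under ventilation with EIT taken after extubation, because the two are not comparable.
- Add a worst-rank sensitivity analysis for both primary endpoints, giving these patients the worst rank in a Mann-Whitney comparison. It should remain a sensitivity analysis, since some causes will not be respiratory.

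The change concerns the analysis population only. It costs a short amendment and a few missing primary values, which use part of the 10% dropout allowance. The sample size stays at 40 per arm: with 38 evaluable per arm the EIT power is 0.925, and with 36 it is 0.911 (Welch), as far as numbers alone are concerned.
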